**Figure 1 F1:**
[figure not shown]
Study flowchart. ICS = Catalan Institute of Health.

### Masking

2.6

The study will be blind for the trial participants, investigators of the project and data managers, but will not be blind to the physicians.

### Data collection

2.7

The study variables will be collected from the SIDIAP population database. The SIDIAP has anonymous data of 5.8 million patients in the electronic medical registry system of the ICS and complementary sources. This database includes the following information: sociodemographic variables, healthcare activity, and clinical variables. Pharmacy registries: Information on the medications provided by pharmacies and the associated cost. Laboratory tests. The anonymized data will be exported from the SIDIAP to the statistical package used in the study.

### Outcomes

2.8

The outcomes of the study are as described below. Health events will be classified according to the International Classification of Diseases-10 code. A schedule for data collection is presented in Table 1.

**Table 1 T1:**
[figure not shown]
Schedule for data collection.

#### Primary outcomes

2.8.1

(1)Incidence rate of thromboembolic events (acute myocardial infarction or angina, ischemic stroke, peripheral embolism, or transient ischemic attack [TIA]).(2)Incidence rates: Hemorrhagic events (intracranial hemorrhage, gastrointestinal hemorrhage); All-cause mortality.(3)Adequacy of anticoagulant treatment: This variable encompasses the adequacy of the anticoagulant treatment, taking into account if an adequate change has occurred or not. The adequacy of the AT in patients with NVAF will be based on the fulfillment of the criteria of the ministry of health, social services and equality of Spain, 2016^[11]^ (Table 2).

**Table 2 T2:**
[figure not shown]
Criteria on the adequacy of treatment with DOACs, according to ministry of health, social services and equality from Spain (2016).

0 = No adequate change (when an inadequate change has been produced or when an inadequate treatment has been maintained).

1 = adequate change (when an adequate change has been produced or when an adequate treatment has been maintained).

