### Intervention

2.3

The clinical decision support tool for improving the adequacy of AT in NVAF (CDS-NVAF) was developed by the ICS in collaboration with primary care physicians in 2017. CDS-NVAF is intended for patients diagnosed with NVAF and treated with VKA. This tool calculates the TTR using the Rosendaal method considering the last INR data. The INR data are found in the clinical history of NVAF patients and are located on the screen of the follow-up of oral anticoagulant use.

The CDS-NVAF will be activated when the physician introduces the last INR value. At this time the TTR will be calculated automatically. If the TTR value is <65%, a pop up screen with an advisory text will open suggesting a change to DOAC therapy. The physician can decide whether to change or not the previous prescription. If the TTR value in >65% the pop up screen will not appear. The TTR value will remain registered on the screen of the follow-up of oral anticoagulant use and can be consulted in future queries.

The diffusion of the CDS-NVAF will be made by an announcement on the first day of the intervention when the healthcare professional opens the electronic clinical history. The professionals of the intervention group will receive the announcement and will be provided with the CDS-NVAF. The professionals who are part of the control group will not receive any of the above described information.

The implementation of the CDS-NVAF, and thus, the beginning of the study is expected to December 15, 2017.

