### Statistical analysis

2.10

The statistical analysis will be performed at 3 time points: before the implementation of the CDS-NVAF (baseline), at 1 year after the beginning of the intervention (1-year follow-up), and at 2 years after the beginning of the intervention (2-year follow-up).

A descriptive analysis of all the variables studied will be carried out using frequency and percentage for categorical variables and mean, standard deviation, minimum, median, and maximum for continuous variables. The Students’ *t* test (or the Mann–Whitney U test in cases not fulfilling the criteria of normality) will be used to determine possible differences in the means of the quantitative variables between the 2 study groups. The Chi-square test (or Fisher exact test) will be used for the qualitative variables. The rates of incidence for each variable will be expressed as patient/years with the corresponding confidence intervals of 95%.

Analysis at a professional level: a logistic regression model will be used to search for possible associations among the primary outcome variables and the secondary variables. First, each variable will be evaluated separately by univariate models and all the variables that are statistically significant or have a *P* ≤ .10 will be included in the multivariate model.

Analysis at a patient level: at this level hierarchal or multilevel methods will be used to take into account the structure of the data and to be able to introduce the variables of the patient in the estimation of the effect of the intervention. The levels will be professional (level 2) and patient (level 1). Multilevel logistic regression models will be made to estimate the effect of the intervention. The strategy of the analysis will be to estimate the effect of the intervention considering professionals as the random part. Afterwards, we will estimate the effect by introducing the variables of quality of care of the professional level (SQPP and SHCQ) and finally, we will study whether the introduction of patient variables modifies the effect of the intervention.

The level of significance will be set at 5% and the statistical package IBM SPSS Statistics v.23.0 for Windows will be used to perform the statistical analyses.

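### The primary adequacy outcome is defined both as a state and as a transition, with no reference date: a patient on unchanged VKA whose TTR crosses 65% can be coded 0 or 1, and the baseline value is undefined

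*Protocol article*

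**What the plan says.** Section 2.8.1 (Primary outcomes) lists adequacy as the third primary outcome and describes it in two ways. One is a state: "The adequacy of the AT in patients with NVAF will be based on the fulfillment of the criteria of the ministry of health". The other is a transition: "taking into account if an adequate change has occurred or not". The coding under Table 2 follows the second: "0 = No adequate change (when an inadequate change has been produced or when an inadequate treatment has been maintained" and "1 = adequate change (when an adequate change has been produced or when an adequate treatment has been maintained". The caption of Table 2 describes its content as "Criteria on the adequacy of treatment with DOACs, according to ministry of health, social services and equality from Spain (2016"; the table itself is not shown.

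Section 2.10 (Statistical analysis) sets the times: "before the implementation of the CDS-NVAF (baseline), at 1 year after the beginning of the intervention (1-year follow-up", and again at 2 years. The intervention effect comes from multilevel logistic regression with professionals as the random part. The professional-level quality scores are added next, and patient variables last.

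The Introduction gives a TTR below 65% as a criterion of poor VKA control. Section 2.3 (Intervention) has the tool recalculate TTR when the last INR is entered, and lets the physician keep the existing prescription. It adds: "The TTR value will remain registered on the screen of the follow-up of oral anticoagulant use and can be consulted in future queries".

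**The concern.** A code built on changed or maintained needs a reference point: adequate or inadequate as judged when? The shown text does not say. The question is harmless if adequacy moves only when the drug changes. It is not harmless here, because TTR is recalculated over time and a patient who stays on VKA can cross 65% in either direction. Such a patient fits both codes.

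This is the primary outcome closest to what the tool acts on. If adequacy is anchored at the start, regained VKA control without a drug change counts as failure, and lost control counts as success. If it is anchored at the time point, the same records give different codes and can give a different effect. A choice left open until outcome data are available weakens the result.

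The baseline analysis has the same gap. Without a defined baseline value the model cannot use one, although only 15 sectors are allocated by simple randomisation (section 2.5), where chance imbalance in baseline adequacy is likely.

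**Working it through.** The plan gives no rate, effect size or power for adequacy, so there is no stated figure to reproduce.

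**1. The coding applied to two patients who keep VKA**

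| TTR at start, then at time point | Judged at start | Judged at time point |
|---|---|---|
| 60%, then 70% | inadequate, maintained: 0 | adequate, maintained: 1 |
| 70%, then 60% | adequate, maintained: 1 | inadequate, maintained: 0 |

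Both readings fit the wording. Section 2.4 counts 63,001 VKA patients among 73,632 treated (63,001 / 73,632 = 85.6%), so the question concerns most of the treated population. How many would cross 65% is not given.

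**2. Baseline.** Section 2.10 has a baseline analysis. The code in section 2.8.1 needs an earlier status to call a treatment changed or maintained, and no look-back period is named.

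**3. Effect on the arm difference.** Every input below is an assumption.

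- b: share of VKA patients below 65% at start (30–50%)
- u: share of those staying on VKA who rise to 65% or above (10–50%)
- d: share of the initially well controlled who fall below 65% (10–30%)
- D: arm difference in switching among patients poorly controlled at start (10 points: 20% versus 10%)
- L: the same difference among patients who fall below 65% later (0, D/2 or D)

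Start-status effect = b·D.
End-status effect = b·(1−u)·D + (1−b)·d·L.
Ratio, end to start = (1−u) + [(1−b)/b]·d·(L/D).

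With b = 40%, the start-status effect is 0.40 × 10 = 4.0 points. The end-status effect is:

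- u = 45%, L = 0: 0.40 × 0.55 × 10 = 2.2 points, ratio 0.55
- u = 45%, d = 20%, L = D/2: 2.2 + 0.60 × 0.20 × 5 = 2.8 points, ratio 0.70
- u = 45%, d = 20%, L = D: 2.2 + 0.60 × 0.20 × 10 = 3.4 points, ratio 0.85
- u = 45%, d = 30%, L = D: 2.2 + 0.60 × 0.30 × 10 = 4.0 points, ratio 1.00
- u = 10%, d = 30%, L = D: 3.6 + 1.8 = 5.4 points, ratio 1.35

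Levels for the first case (d = 20%, no late switching in either arm): start-status 64.0% versus 68.0%; end-status 68.2% versus 70.4%.

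**4. Grid.** Taking b at 30, 40, 50%; u at 10, 20, 30, 40, 50%; d at 10, 20, 30%; and L at 0, D/2, D gives 3 × 5 × 3 × 3 = 135 settings. The ratio runs from 0.5 (u = 50%, L = 0) to 1.6 (b = 30%, u = 10%, d = 30%, L = D: 0.90 + 2.333 × 0.30 = 1.6). It is at or below 0.60 in 22 settings (16%), equals 1 in 5 and exceeds 1 in 31 (23%).

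**5. A convention behind this range.** The start-status formula counts a patient who was well controlled at start as 1 even if switched later. If that late switch were instead coded as an inadequate change, the start-status effect would be b·D − (1−b)·d·L. With b = 40%, d = 30%, L = D this is 4.0 − 1.8 = 2.2 points, against 4.0 on end status with u = 45%. The range is therefore illustrative and not an outer bound.

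**The case against.** **The text can be read coherently.** If adequacy is judged at follow-up, codes 0 and 1 are exhaustive and exclusive, and the reference to fulfilling the criteria supports that reading. This is fair, but the change-and-maintained wording equally supports judging at the start, and nothing shown chooses between them.

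**Dates and windows of derived variables are often left to a fuller document.** The article cites a protocol version that is not shown, and Tables 1 and 2 are missing from the text. A request for a reference date alone would indeed only ask for omitted detail. What remains is that the article does print a coding rule, the rule permits two values for the same patient, and the model described can be improved at almost no cost.

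**Baseline.** A reader might infer that the outcome cannot have a baseline value. The documents do not support that. Section 2.2.1 requires at least 6 INR controls in the year before the intervention, so maintained could be scored over that year. The value is undefined, not impossible.

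**Adjustment.** Section 2.10 admits patient variables and excludes none, so adjustment for baseline adequacy is not ruled out. It is simply not named.

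**Size.** A reader might infer that the effect would nearly halve. That needs u of about 45% or more and little or no tool effect on patients who fall below 65% later. Section 2.3 triggers the alert at any INR entry with TTR below 65%, so those patients are alerted too.

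**Conclusion.** The point holds as an ambiguity in the meaning of a primary outcome. The shown text supports both a state and a transition, a patient on unchanged VKA who crosses 65% can be coded either way, the baseline value is not defined, and the models described do not name baseline adequacy.

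It is not a demonstrated bias in a known direction. The 0.5 to 1.6 range rests entirely on assumed control, crossing and switching rates, and on treating late switches as neutral under start-status coding. Near-halving is one case within that range; no difference, or a larger effect, are others. The point is worth settling before outcome data are seen, and the unseen tables should be checked for a reference date first.

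**What to change.** In section 2.8.1, replace the change/maintained code with a yes/no state: does the treatment in use at the time point meet the Table 2 criteria? Score it in the same way at baseline, 1 year and 2 years. State that patients already switched to DOAC are judged on their control before the switch. They no longer have a current TTR on VKA, so without this rule the state is undefined for the patients the tool aims to move.

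In section 2.10, estimate the intervention effect on the 1- and 2-year state with baseline adequacy as a covariate. Report the four categories (adequate change, inadequate change, adequate maintained, inadequate maintained) descriptively by arm.

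The cost is a few sentences, one covariate and slightly more derivation work. It needs INR and prescription histories at each time point; section 2.7 lists laboratory and pharmacy data in SIDIAP, but Table 1 is not shown, so this should be confirmed. The arm difference may look smaller or larger than under start-anchored coding.

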#### Secondary outcomes

2.8.2

(1)Sociodemographic characteristics of the patients: age, sex, primary care area assigned, physician assigned;(2)PCC characteristics: teaching center, urban/rural, socioeconomic deprivation index (MEDEA), standard of healthcare quality (SHCQ) and the standard of quality of pharmaceutical prescription (SQPP);(3)Characteristics of the professional: age, sex, PCC, type of work contract, SHCQ, SQPP;(4)Type of anticoagulant treatment: DOAC (dabigatran, apixaban or rivaroxaban), VKA (acenocoumarol or warfarin), heparin (with starting and completion date);(5)Type of treatment with risk of bleeding: antiaggregants, nonsteroidal anti-inflammatories, and selective serotonin reuptake inhibitors (with starting and completion date);(6)Thromboembolic risk CHA2DS2-VASC (congestive heart failure, hypertension, age 75 years or older, diabetes mellitus, previous stroke or TIA, vascular disease, age 65–74 years, female) score (with date of determination). The score indicates the risk of a patient with NVAF of suffering a stroke in 1 year. The score goes from 0 (absence of risk) to 10 (greater risk);(7)Bleeding risk HAS-BLED (hypertension, abnormal liver/renal function, stroke, bleeding history or predisposition, labile INR, elderly (>65 years), and drugs/alcohol) score (with date of determination). The score allows the calculation of the risk of bleeding in patients with NVAF receiving oral anticoagulant treatment based on the risk factors associated with the probability of bleeding. Score: 0 = low risk; 1 = intermediate risk; 2 = intermediate risk; ≥3 = high risk;(8)Associated comorbidity (with date of diagnosis): diabetes mellitus, arterial hypertension, heart failure, chronic kidney failure, nephropathy, abnormal liver function, alcoholism, peripheral vascular disease, stroke, peripheral embolism, or TIA;(9)Other determinations (with date of determination): creatinine, systolic blood pressure, and ejection fraction.

### Pilot study

2.9

To evaluate the initial functioning of the CDS-NVAF and to promote technical improvements before the beginning of the study, a pilot study was carried out for 15 days (from July 20, 2017 to August 3, 2017). The pilot study consisted in the evaluation of 3 PCCs, 2 of which received the alert in the electronic clinical history with the characteristics described in the ‘intervention’ section.

During the period of the pilot study, aspects about the functionality of the CDS-NVAF and suggestions for improvements were collected from the research team and the primary care professionals (physicians, nurses, and referent professionals) in work meetings. Some changes and suggestions for improvements on the part of professionals were incorporated to improve the functionality of the CDS-NVAF.

### Statistical analysis

2.10

The statistical analysis will be performed at 3 time points: before the implementation of the CDS-NVAF (baseline), at 1 year after the beginning of the intervention (1-year follow-up), and at 2 years after the beginning of the intervention (2-year follow-up).

A descriptive analysis of all the variables studied will be carried out using frequency and percentage for categorical variables and mean, standard deviation, minimum, median, and maximum for continuous variables. The Students’ *t* test (or the Mann–Whitney U test in cases not fulfilling the criteria of normality) will be used to determine possible differences in the means of the quantitative variables between the 2 study groups. The Chi-square test (or Fisher exact test) will be used for the qualitative variables. The rates of incidence for each variable will be expressed as patient/years with the corresponding confidence intervals of 95%.

Analysis at a professional level: a logistic regression model will be used to search for possible associations among the primary outcome variables and the secondary variables. First, each variable will be evaluated separately by univariate models and all the variables that are statistically significant or have a *P* ≤ .10 will be included in the multivariate model.

Analysis at a patient level: at this level hierarchal or multilevel methods will be used to take into account the structure of the data and to be able to introduce the variables of the patient in the estimation of the effect of the intervention. The levels will be professional (level 2) and patient (level 1). Multilevel logistic regression models will be made to estimate the effect of the intervention. The strategy of the analysis will be to estimate the effect of the intervention considering professionals as the random part. Afterwards, we will estimate the effect by introducing the variables of quality of care of the professional level (SQPP and SHCQ) and finally, we will study whether the introduction of patient variables modifies the effect of the intervention.

The level of significance will be set at 5% and the statistical package IBM SPSS Statistics v.23.0 for Windows will be used to perform the statistical analyses.

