Despite the increasingly more frequent use of computerized medical reminders, few studies have assessed their impact on health outcomes.^[17–21]^ A systematic review showed that notifications influence specific aspects of the prescription process and may be an effective method to reduce the prescription of contraindicated medications, although their impact on health outcomes was not demonstrated.^[22]^ Within the primary care setting it was found that computerized clinical notifications significantly improved the adequacy of treatment in patients with poorly controlled asthma and consequently reduced the rate of reexacerbations during follow-up. Moreover, medical professionals considered these reminders to be particularly useful for the identification of patients with bad control.^[23]^

The present project aims to evaluate the impact of the implementation of a clinical decision support tool associated with the electronic clinical history which informs healthcare professionals of the TTR in patients with NVAF attended in primary care centers (PCCs) of the ICS. This project will evaluate the impact of this tool on the adequacy of anticoagulant treatment, the incidence of thromboembolic and hemorrhagic complications, and mortality at 2 years after the beginning of the intervention. The evaluation of the impact of the intervention will be performed based on the characteristics of the patients and the healthcare professionals.

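### Univariate P ≤ .10 screening into a logistic model with no stated cluster term makes the exploratory professional-level associations less reliable than their 5% P values suggest

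*Protocol article*

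**What the plan says.** Section 2.10 (Statistical analysis) describes two analyses.

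At professional level, "a logistic regression model will be used to search for possible associations among the primary outcome variables and the secondary variables". The selection rule is explicit: "First, each variable will be evaluated separately by univariate models and all the variables that are statistically significant" go forward to a joint model, as does any variable whose univariate P value is at most .10. Significance for the study is set at 5%. No random effect, cluster term or robust error is mentioned for this model.

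At patient level, hierarchical methods are brought in because of the structure of the data, with professional as level 2 and patient as level 1. This is where the treatment effect is obtained: "Multilevel logistic regression models will be made to estimate the effect of the intervention". Covariates enter that model in a stated order: professionals as the random part, then the quality scores SQPP and SHCQ, then patient variables.

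The variables available for screening are listed in section 2.8.2 (Secondary outcomes). Five are characteristics of the PCC (teaching status, urban or rural, deprivation index, SHCQ, SQPP). Six are listed for the professional, or five once the PCC identifier is left out. The rest are mainly patient variables. No model in the article has a PCC or sector level, although section 2.5 randomises 15 sectors.

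**The concern.** Two separate problems meet in this step.

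The first is selection. Variables are chosen because their P value in these data is small, and the same data then supply the P values of the multivariate model. Those P values are read at 5% as if the list had been fixed beforehand.

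The second is clustering. A PCC characteristic takes one value for everyone in the centre, and a professional's age or contract type takes one value for all of that professional's patients. If outcomes vary between centres or professionals for other reasons, a model that treats the rows as independent gives standard errors that are too small for such variables. They then pass the screen, and reach 5% in the final model, too often.

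At stake is the credibility of any association reported between the outcomes and the type of centre, deprivation, quality scores or professional characteristics. Section 2.11 plans to present results to the institute's own professionals, so a spurious association could be taken as a finding about centres or doctors.

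**Working it through.** The article gives no figure for this step, so there is nothing of its own to reproduce. The check asks how often a characteristic unrelated to the outcome would get through.

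**Inputs from the article**
- 287 PCCs (section 2.1)
- 63,001 patients on VKA and 73,632 anticoagulated in all (section 2.4)
- entry threshold P ≤ .10 and significance level 5% (section 2.10), taken as two-sided
- 5 PCC and 5 professional characteristics (section 2.8.2)

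**Assumptions, because the article does not give them**
- ICCs
- patients per professional and professionals per PCC
- whether a row is a patient or a professional

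**Formulas.** Design effect DE = 1 + (m − 1) × ICC, where m is the number of rows sharing one value of the characteristic. The chance that a null characteristic passes a model that ignores clustering is 2 × [1 − Φ(1.645/√DE)] at P ≤ .10, and 2 × [1 − Φ(1.96/√DE)] at P < .05.

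**Reading A: one row per patient.** For a PCC characteristic, m = 63,001/287 = 219.5.

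| Assumed ICC | DE | Passes P ≤ .10 |
|---|---|---|
| 0.005 | 2.1 | 26% |
| 0.01 | 3.2 | 36% |
| 0.02 | 5.4 | 48% |
| 0.05 | 11.9 | 63% |

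The chance of P < .05 runs from 18% to 57% over the same range. Using all 73,632 patients (about 257 per PCC) changes little: 38% pass at ICC 0.01 and 66% at 0.05. Both counts precede the eligibility criteria, which lower m and so the inflation.

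For a professional characteristic with an assumed m = 20, ICC 0.01 gives DE = 1 + 19 × 0.01 = 1.19 and a pass rate of 13%. ICC 0.05 gives DE = 1.95 and 24%.

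**Reading B: one row per professional.** Clustering of patients then no longer distorts professional characteristics; what remains is professionals within PCCs. For a PCC characteristic with an assumed m = 10:

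| Assumed ICC | DE | Passes P ≤ .10 |
|---|---|---|
| 0.001 | 1.009 | 10% |
| 0.01 | 1.09 | 11.5% |
| 0.05 | 1.45 | 17% |
| 0.10 | 1.90 | 23% |

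**Selection alone, with valid P values.** Ten independent null candidates give 1 − 0.90^10 = 65% for at least one passing the screen, and 1 − 0.95^10 = 40% for at least one P < .05, per outcome and analysis. If the final P value is close to the univariate one, a null that has entered the model has about a 0.05/0.10 = 50% chance of showing P < .05.

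**Simulation of screen then refit.** Reading A, 300 runs per setting. Assumed: 287 PCCs, 10 professionals each, 26 patients each, a 30% outcome rate, and 5 PCC and 5 professional null covariates.
- No clustering: 11% to 12% selected and 5% to 6% with final P < .05 per variable; at least one false association in 42% of runs; 48% of the selected nulls had final P < .05.
- ICC of about 0.012 to 0.048 at each level: PCC nulls had final P < .05 in 28% to 53% of cases and professional nulls in 11% to 22%; at least one false association in 89% to 100% of runs.

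So clustering makes the individual P values too small, while the screen adds selection and multiplicity that a cluster-aware model alone would not remove.

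**The case against.** The case on the other side has several parts, and much of it stands.

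*The unit of analysis is not stated.* The step is titled as a professional-level analysis and contrasted with a patient-level one. With professionals as rows and an ICC of 0.01, the pass rate for a null PCC characteristic is 11.5%, hardly above the intended 10%. This stands. A binary patient outcome fits awkwardly with one row per professional, so neither reading can be ruled out. The 26% to 63% range must not be quoted without its condition.

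*The model is never called single-level.* That is an inference from the contrast between the two paragraphs, and standard-error handling can be left to a fuller document. This is fair as to the cluster term. It does not touch the screening rule, which the article fixes explicitly.

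*A reader might count more than 30 candidates and infer a 79% chance of a false association* (1 − 0.95^30 = 0.785). The list does not support this. The stroke-risk score is built from age, sex, diabetes, hypertension and other items that are also listed separately, so the candidates are not independent. By the article's own description the risk scores relate to stroke and bleeding, so they are not nulls. The patient variables also appear to belong to the patient-level model. About ten candidates is the defensible count.

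*A reader might infer that the trial's treatment effect is at risk, for instance through confounders dropped by the screen.* The article does not say so. The effect comes from the separate multilevel model with a stated order of entry, and the screen does not feed it. The Introduction does promise that "The evaluation of the impact of the intervention will be performed based on the characteristics of the patients and the healthcare professionals", but the multilevel sequence serves that aim more directly; the professional-level paragraph does not mention the intervention.

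*A reader might argue that so many patients make screening needless.* Events govern here: 63,001 × 0.0066 is about 416 thromboembolic events if the rate in section 2.4 is read as a risk over the analysis period. That is modest for 30 or more terms, but about 42 per term for ten.

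**Conclusion.** The point holds in a limited form. The article fixes a P ≤ .10 univariate screen into a logistic model judged at 5%, with no cluster term stated, while it recognises the data structure at patient level. The final P values ignore the selection on any reading, and on the natural reading they also ignore the nesting in PCCs.

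The clustering part ranges from negligible (one row per professional, low ICC) to serious (one row per patient, PCC-level variable). It rests on assumed ICCs and cluster sizes throughout. The selection part does not depend on those assumptions: roughly a 40% chance of at least one false association with ten independent null candidates.

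The wording of the step, a search for possible associations, is exploratory, and the harm is confined to those associations. This is a minor but worthwhile improvement, not a threat to the randomised comparison.

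**What to change.** In section 2.10, delete the univariate screening step. Name in advance a short list of professional and PCC characteristics, measured before the tool is activated, since quality-of-prescribing scores could themselves move once it is running. Enter them together in a multilevel logistic model with random effects for professional and PCC, or use cluster-robust errors at the level where each characteristic varies. State the unit of analysis. Report estimates with 95% confidence intervals and label them exploratory.

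Both halves are needed: the cluster-aware model deals with the standard errors, and the fixed list deals with the selection. A fixed list of ten still gives a 40% chance of at least one false P < .05 if all are null and independent, which is why the exploratory label and the short list matter.

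The cost is a change of wording and one modelling step fewer. The small downside is that the covariate list must be agreed before data extraction.
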